### Sample size

Based on the data from the pilot study in 46 babies and using the same analysis technique of nicotine in hair used in the present study, a mean of 6.83 ng/mg and a standard deviation of 8.88 ng/mg have been obtained. Assuming a mean difference of 30% between the intervention group and the control group in nicotine in hair at the end of the intervention, with an alpha value of 0.05 and a power of 80%, 295 subjects are needed in each group. If we assume a loss of 20%, the sample size increases to 708 (354 in each group). It is considered feasible for each basic care unit to recruit eight babies in a period of two months. The estimates of the intra-cluster correlation coefficient in cluster randomized trials that evaluate the implementation of clinical practice guidelines using outcome variables in primary healthcare are generally less than 0.05 [34]. These intra-cluster correlation coefficients translate to a cluster size of eight in a design effect corresponding to a factor of 1.4. Therefore, the final simple size will be 992 babies (446 in each group).

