### Data collection procedures

There will be three visits with each baby included in the study in both, control and intervention group: a visit at the start of the study (recruitment) and two follow-up visits, at three and six months after the recruitment visit (Figure 1).

The father and/or mother will be asked to provide, using an electronic data collection system created for the study, data regarding the following:

1-The baby: age, sex, breastfed/artificial milk, living nucleus, medical history and clinical data for follow-up,

2- The parents: age, sex, socio-demographic data, smoking status (yes or no). In smokers, data on the smoking habit, smoking behavior during pregnancy and whether or not the baby was breastfed, behavior during breastfeeding. Finally, smoking behavior changes during the study.

3-The degree of exposure of the baby to ETS, within and outside of the home, will be based on the questions proposed by clinical practice guidelines [13,14,35,36].

In order to measure the levels of biological nicotine in hair, a sample of the baby's hair will be taken at the first (recruitment) visit and at the last (six-month) visit. A lock of hair will be cut from the root and once collected, will be placed on a card and put into an envelope, which will be provided with the study materials (Additional files 1 and 2).

For the secondary objective, change in smoking habit in the father and/or mother, expired carbon monoxide will be measured in those that declare smoking abstinence during the study period. Cut off point: 10 ppm.

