### Statistical analysis

Statisticians from the University of Girona's Research Group in Statistics, Applied Economics and Health (GRECS) will carry out the statistical analyses. These statisticians will have an advisory role.

The data will be incorporated into a database constructed using SPSS version 15.0. The descriptive analyses, as well as the statistical hypothesis testing, will also be conducted with this program. For subsequent modeling, the Free R software (version 11.0 or later) will be used.

All of the known potential confounding factors will be measured at the beginning of the study, including the caretaker who smokes (and the stage of change), level of education, marital status, breastfeeding and other members of the household, overcrowding. Therefore, the control and intervention group comparisons will be carried out both adjusted and unadjusted for these known confounders.

The simple treatment effect without adjusting the rates, relative risks and the 95% confidence intervals will be obtained in the first case, with a subsequent adjusted multiple regression analysis for other variables. Two forms of regression analysis will be taken into account for the primaries.

Expected results: A Poisson regression analysis and a negative binomial if there is evidence of over or under dispersion. The analysis of the secondary results will be carried out using standard statistical procedures applicable to categorical or continuous data. An adjustment for protocol analysis will also be conducted to verify the robustness of the results. All tests of significance will be two-tailed. For the treatment effects, sensitivity analyses will be conducted to determine the effect of the missing data.

The analysis will be done following the following study phases:

1. Describe the effect in both groups:

Initially an analysis of baseline comparability will be carried out in relation with the study variables. The following step will be to estimate the effect on the response variables without adjusting for other variables. To perform the above analyses, chi-squared tests will be used for qualitative variables and comparison of means for quantitative variables.

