2. To estimate the adjusted effect, a multivariate multilevel model will be used. The dependent or principal variable is the child's exposure using the measure of nicotine in hair. The baby's age and sex, as well as the variables that have been shown to be statistically significant, will be included in the bivariate analyses. The basic care unit and the individual will be the levels in the multilevel analysis.

3. Concordance between the filled questionnaire and the nicotine collected in the hair: a summary evaluation of the questionnaire on a discrete, quantitative scale based on the data that is provided by the number of smoking cohabitants, the number of cigarettes that they smoke and the exposure time outside of the home. Pearson's (or Spearman's depending on the distribution) correlation coefficient will be calculated between the estimate and the result obtained in the nicotine hair analysis. The intraclass correlation coefficient will also be studied between both measures. Finally, both estimates will be dichotomized (questionnaire and nicotine in hair analysis) into two categories (exposed/not exposed) and the Kappa coefficient between the two will be calculated.

In all cases a bilateral alpha error of 0.05 and a 95% confidence interval will be used. To complete the explicit information, the comparison of means will be performed using a Student's t-test for parametric variables and the U Mann-Whitney test for non-parametric variables.

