## Results

Primary results to obtain:

Reduction of exposure to ETS measured at the beginning of the intervention (recruitment phase) and at six months, using a questionnaire that includes information about ETS history during pregnancy and breastfeeding, exposure to ETS within and outside of the home, family smoking habits and measures used to avoid exposure. To develop this questionnaire, questionnaires used in similar studies have been adapted (varying some items, based on the results of the pilot study). As an objective measurement of the exposure: biological levels of nicotine in hair of babies. All of the hair samples (from the pilot test and the definitive study) will be analyzed by the same team at IMIM.

Secondary results to obtain:

- Reduction or cessation of smoking habit in parents, measured using a questionnaire about status of the smoker/ex-smoker/non-smoker and using the Fagerström Nicotine Dependence Test in those that smoke, as well as the stage of change (pre-contemplation, contemplation, preparation, action, maintenance, finalization). In smokers that declare smoking abstinence, the amount of carbon monoxide in expired air will be determined (Smokerlyzer). Cut-off point: 10 ppm.

-Other variables using questionnaire/clinical records, including data related to:

Type of professional that performs the intervention: pediatrician, pediatric nurse or both.

The baby: age, sex, breastfeeding, medical history, living nucleus.

The father and/or mother that attends the visit: age, sex, marital status, socioeconomic situation.

Parents' level of knowledge and their level of risk perception to exposure.

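### Adjustment for baseline hair nicotine is left to a significance screen, and the main model gives no time point for its outcome

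*Protocol article*

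**What the plan says.** All references are to the protocol article.

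- **Data collection procedures:** the baby's "hair will be taken at the first (recruitment) visit and at the last (six-month) visit". A baseline measurement of the outcome is thus planned for each baby.
- **Sample size:** the calculation is worded "Assuming a mean difference of 30% between the intervention group and the control group in nicotine in hair at the end of the intervention". It uses the pilot figures ("a mean of 6.83 ng/mg and a standard deviation of 8.88 ng/mg have been obtained") and has no baseline term, so it concerns an unadjusted final value.
- **Statistical analysis, phase 2:** the dependent variable of the multilevel model is the child's "exposure using the measure of nicotine in hair". Neither a time point nor a choice between level and change is given. Age and sex are named as covariates; other variables enter according to statistical significance in bivariate analyses. The text does not say what is tested against what.
- **Statistical analysis, list of confounders:** baseline nicotine is not named. The list is introduced as a set of examples, so it is not exhaustive.
- **Results, primary results:** the section opens with "Reduction of exposure to ETS measured at the beginning of the intervention (recruitment phase) and at six months", and the sentence goes on to a questionnaire. Hair nicotine follows in a separate sentence, as a level that serves as the objective measure of exposure.

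**The concern.** The baseline value of a continuous outcome is usually among its strongest predictors, and here it is collected in any case. A rule that fixes age and sex but leaves baseline nicotine to a significance screen puts that information at the mercy of how the screen is read. If candidates are tested for a difference between arms, a sizeable but non-significant baseline difference would go unadjusted.

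This trial has some reason to expect imbalance. It is open, teams are allocated before they recruit their babies, and some exclusions rest on the professional's judgement.

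The missing time point adds a second uncertainty. The three sections describe the outcome differently enough that an analyst would have to settle the definition alone.

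**Working it through.** **Inputs from the article.** Mean 6.83 and SD 8.88 ng/mg; 30% difference; "with an alpha value of 0.05 and a power of 80%, 295 subjects are needed in each group"; two-sided testing ("All tests of significance will be two-tailed"); 20% loss; design effect 1.4; 992 babies in total.

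**Assumptions, not in the article.** Correlation r between baseline and six-month nicotine of 0.3 to 0.7; equal SDs at both times; a linear model on the raw scale; the design effect of 1.4 applies with and without adjustment.

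**1. The plan's own figure.** The target difference is 0.30 × 6.83 = 2.049 ng/mg. Then n per arm = 2 × (1.960 + 0.842)² × 8.88² / 2.049² = 295 after rounding up, as stated. Next, 295 × 1.2 = 354 per arm, which agrees with "If we assume a loss of 20%, the sample size increases to 708 (354 in each group"), and 708 × 1.4 = 991.2, rounded to 992. The calculation is therefore for an unadjusted six-month comparison.

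**2. Power of that comparison at 992 babies.** Half of 992 is 496 per arm. (The article prints 446 per group, which does not add up to 992; that is a separate matter.) Effective number per arm = 496 × 0.8 / 1.4 = 283. SE = 8.88 × √(2/283.4) = 0.746. Power = Φ(2.049/0.746 − 1.96) = 78%. The small shortfall from 80% arises because loss was allowed for by multiplying by 1.2 rather than dividing by 0.8.

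**3. The same comparison adjusted for baseline.** The residual variance is (1 − r²) times the original, so the SE becomes 0.746 × √(1 − r²).

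| r (assumed) | Variance reduction r² | Power, unadjusted | Power, baseline-adjusted | n per arm before inflation |
|---|---|---|---|---|
| 0.3 | 9% | 78% | 82% | 269 |
| 0.5 | 25% | 78% | 89% | 222 |
| 0.7 | 49% | 78% | 97% | 151 |

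If 446 per arm were the true figure, power would be 74% unadjusted and 78%, 85% and 95% adjusted. The pattern is the same.

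**4. Baseline imbalance.** All 992 babies count at recruitment, so the effective number per arm is 496 / 1.4 = 354. The SE of the baseline difference is 8.88 × √(2/354.3) = 0.667 ng/mg. A difference of up to 1.96 × 0.667 = 1.3 ng/mg would be non-significant; that is 1.308 / 2.049 = 64% of the target effect. With equal SDs, a fraction r of it carries over to six months: 0.3 × 1.308 = 0.4 up to 0.7 × 1.308 = 0.9 ng/mg, or 19% to 45% of the target. A between-arm significance screen would leave this in the estimate; a fixed baseline covariate would remove it.

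**The case against.** **The existing rule may already bring baseline nicotine in.** The covariate sentence is garbled, but its most natural reading is that variables significantly related to the outcome enter the model. About 992 × 0.8 = 793 babies would be followed. At r = 0.3, t = 0.3 × √791 / √0.91 = 8.8, or about 7.5 with an effective number of about 566. If baseline nicotine were a candidate in such a screen, it would pass almost certainly, and most of the gain in the table would follow under the present plan. This stands, and it limits the point to a gain that is not guaranteed.

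**The outcome may not really be contradictory.** A reader might infer that the primary analysis is a change score. With SD × √(2(1 − r)), that would have power of 64%, 78% and 94% at r = 0.3, 0.5 and 0.7, so below plan when r is under 0.5. The document does not support this inference. Reduction is tied first to the questionnaire, nicotine is named as a level, and no section prescribes a change score for nicotine. What remains is loose wording and a missing time point.

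**An article condenses.** A full covariate list may be left to a fuller document, and the list of confounders is open-ended. But the article states its own covariate rule, and that rule names two fixed variables without the baseline outcome. The point concerns a rule as stated, not an omitted detail.

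**Conclusion.** The point holds in a limited form. Baseline hair nicotine is planned for each baby, but the stated model does not guarantee its use, and the model's outcome lacks a time point.

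Under r of 0.3 to 0.7, equal SDs and the plan's own loss and design effect, fixing the covariate would cut the variance by 9% to 49% and raise power from about 78% to about 82% to 97%. It would also remove the effect of measured baseline differences, including non-significant ones of up to about 1.3 ng/mg.

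Two stronger conclusions might be drawn, and neither is supported:

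- **That the trial loses its planned power.** It does not: the unadjusted six-month comparison stays close to 80%, and the matter is one of efficiency forgone.
- **That baseline adjustment would deal with selective recruitment by teams that know their arm.** It corrects measured differences in nicotine only. Under proper randomisation and recruitment, the unadjusted comparison is not biased on average.

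The size of the gain depends on r, which the article does not give, and on the raw scale; another scale would give other figures.

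**What to change.** - **Statistical analysis, phase 2:** name six-month hair nicotine as the dependent variable. Include baseline hair nicotine, on the same scale as the outcome, as a fixed covariate beside age and sex, whatever its significance.
- **Sample size and Results:** use the same definition in both places, so that the reduction sought is understood as a between-arm difference in six-month nicotine.

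The cost is a sentence or two of text. The baseline sample is already planned, so no further data are needed, and the sample size need not change.

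Selective recruitment needs its own attention and should not be regarded as settled by this change.

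### The Statistical analysis section gives two unreconciled covariate rules for the adjusted effect on hair nicotine, one of them settled by significance in the trial's own data

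*Protocol article*

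**What the plan says.** All the relevant text is in the Statistical analysis section of the protocol article.

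- **Named confounders.** The general paragraphs say that known potential confounders will be measured at the start, "including the caretaker who smokes (and the stage of change), level of education, marital status, breastfeeding and other members of the household, overcrowding". It follows that "the control and intervention group comparisons will be carried out both adjusted and unadjusted for these known confounders". No significance condition is attached. The word that opens the list leaves it open to additions.
- **Phase 1.** "Initially an analysis of baseline comparability will be carried out in relation with the study variables". Unadjusted effects on the response variables come next. Chi-squared tests and comparisons of means serve both steps.
- **Phase 2.** "To estimate the adjusted effect, a multivariate multilevel model will be used". Its outcome is the principal one: "The dependent or principal variable is the child's exposure using the measure of nicotine in hair". The covariate rule names the age and sex of the baby, "as well as the variables that have been shown to be statistically significant, will be included in the bivariate analyses".
- **Level.** "In all cases a bilateral alpha error of 0.05 and a 95% confidence interval will be used".

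Taken literally, the phase 2 rule puts variables into the bivariate analyses. It stands in a paragraph that defines the adjusted model, after an unadjusted phase. The sensible reading is therefore that age, sex and the variables significant in bivariate analyses enter the multilevel model. This point uses that reading.

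**The concern.** The two rules can give different models for the same quantity. The first adjusts for the named confounders whatever the data show, but does not name age and sex. The second guarantees age and sex, and nothing else. It does not say whether a named confounder that fails the screen stays in, nor what the variables must be significant against.

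Three things are at stake:

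- The covariate set for the adjusted analysis of the principal outcome is fixed only after the data have been examined.
- Two analysts who both follow the document can report two adjusted effects, with no stated priority between them.
- Depending on how the screen works, covariates that would sharpen the estimate may be left out.

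**Working it through.** **1. Scale of the trial.** Pilot mean 6.83 and SD 8.88 ng/mg, a 30% difference, two-sided alpha 0.05, power 80% (Sample size section). The difference is 0.30 × 6.83 = 2.049 ng/mg, or 2.049 / 8.88 = 0.23 SD. Then n = 2 × (1.960 + 0.842)² × 8.88² / 2.049² = 294.8, so 295 per group, as the plan states. The checks below use an effect of 0.23 SD and about 300 per arm to match.

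**2. The two rules side by side.**

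| | General paragraphs | Phase 2 |
|---|---|---|
| Age and sex | not named | always in |
| Named confounders | in, unconditionally | in only if significant |
| Other variables | list left open | in if significant |
| Significant against what | does not apply | not stated |

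The named confounders can be counted as seven: smoking caretaker, stage of change, education, marital status, breastfeeding, other household members, overcrowding.

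**3. How unstable is a 0.05 screen?** If seven candidates are unrelated to the screening variable and independent, the chance that at least one passes is 1 − 0.95⁷ = 30%. In the other direction, take 2 × 295 = 590 evaluable babies and ignore clustering. The Fisher z approximation, Φ(atanh(r) × √587 − 1.96), gives the chance that a covariate truly correlated r with outcome passes: 23% at r = 0.05, 49% at 0.08, 68% at 0.10, 96% at 0.15. Weak to moderate covariates come and go by chance.

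A simulated null cluster trial shows the same. It assumed 124 teams (992 / 8) with 6 babies each, intra-cluster correlation 0.05, seven candidates of which three were prognostic at 0.12 SD, and 1,500 runs. Screening on outcome produced 40 different covariate sets, with the truly prognostic set chosen in 58% of runs. Screening on arm imbalance produced 42.

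**4. Type I error in that cluster simulation.**

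| Screen | Selected set | Fixed set | Whichever is significant |
|---|---|---|---|
| Outcome | 6.1% | 6.2% | 6.5% |
| Arm imbalance | 5.7% | 6.4% | 7.3% |

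Selection by itself does not raise the error above that of the fixed set. Freedom to report either model adds 0.3 to 0.9 points to the fixed-set rate.

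**5. Power against a fixed list.** Assumptions: 300 per arm, seven independent covariates each correlated r with outcome, effect 0.23 SD, no clustering. For the fixed list, power is about Φ(0.23 × √150 / √(1 − 7r²) − 1.96). This gives 81% at r = 0.05, 83% at 0.1 and 91% at 0.2, against 80% unadjusted. Simulation (6,000 runs per row, standard error about 0.5 point) adds the two screens:

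| r | Unadjusted | Arm screen | Outcome screen | Fixed list |
|---|---|---|---|---|
| 0.05 | 80% | 80% | 80% | 80% |
| 0.1 | 80% | 80% | 81–82% | 82% |
| 0.2 | 80% | 81% | 90–91% | 90–91% |

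The arm screen loses about 0, 2 and 9 points. The outcome screen loses between 0 and 1 point, because at r = 0.2 it keeps almost all seven covariates (6.99 on average) and at r = 0.05 there is little to gain. With no true effect, rejection stayed at 4% to 5.4% for every method.

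**The case against.** Several points on the other side are sound and limit the finding.

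- **Arm imbalance as the screen.** A reader might infer that covariates are chosen for chance imbalance at baseline, because baseline comparability is the covariate comparison phase 1 describes. Phase 2 does not say so. Its preceding sentence names hair nicotine as the dependent variable, so screening against outcome is at least as natural. The larger power loss belongs to the imbalance reading alone, and only with strong covariates: seven independent ones at r = 0.2 imply 7 × 0.04 = 28% of variance explained, which nothing in the document supports.
- **Inflated false positives.** A reader might infer that choosing covariates by significance damages the test. None of the simulations shows this for either screen.
- **A closed list overridden.** A reader might say that phase 2 replaces a fixed set. The named list is open, and phase 2 is silent on listed confounders that prove non-significant. The rules are unreconciled; one does not expressly cancel the other.
- **The garbled sentence.** The conflict rests on its evident rather than literal meaning. The literal wording would leave the adjusted model with no stated covariate rule, so it needs repair in any case.
- **A condensed article.** Detail left to an analysis plan would be no finding. Here the article itself states two rules that disagree.

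The promised unadjusted comparison does not depend on covariate choice, which limits the damage. It does not settle which adjusted result is meant.

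**Conclusion.** The point holds as a conflict between two stated rules, one of them data-driven, for the adjusted analysis of the principal outcome. The supported harm is a model settled after the data are seen, two possible adjusted results, and a possible loss of precision. That loss ranges from nil to about 9 points of power. The top of the range requires both screening on arm imbalance and an assumed correlation of 0.2 for each of seven independent covariates; at 0.1 the same screen costs about 2 points. Under outcome screening the loss is at most about 1 point. No bias or inflated type I error is shown, and no sample size figure changes. It should be corrected because the text is contradictory and the repair is cheap. It does not invalidate the design.

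**What to change.** Replace the phase 2 covariate sentence with wording such as: *the multilevel model will include arm, the baby's age and sex, and the known confounders listed above, regardless of statistical significance.* Close the list by naming every variable in it.

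Baseline hair nicotine is already measured at recruitment (Data collection procedures section) and can be added to the fixed list to gain precision. That is an optional improvement and is not needed to resolve the conflict. Baseline comparability tests may stay as description, provided the text says they do not decide which covariates enter.

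The cost is one sentence. The variables are already to be collected, and even the 590 evaluable babies counted before the clustering allowance easily carry about ten covariates.

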### Objectives

The principle objective of the BIBE study is to determine the effectiveness of a brief intervention directed at fathers and/or mothers that smoke in order to reduce ETS in babies, in the context of pediatric visits in primary care.

The secondary objectives of the BIBE study are to determine if this intervention produces changes in the tobacco consumption of the parents and subsequently, to study the concordance between the subjective measures of ETS and the objective measures (questionnaire versus biological analysis of nicotine in hair).

The specific objective of this article is to describe the protocol of the BIBE study.

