### Inclusion criteria

Babies under 18 months of age whose parents answer affirmatively to the question "Do you or your partner smoke?" and who give their informed consent to participate in the study.

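### The planned intraclass correlation between the questionnaire score and hair nicotine depends on the arbitrary scale of the score, so it cannot be read as agreement

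*Protocol article*

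**What the plan says.** The Objectives section of the Protocol article includes a secondary aim "to study the concordance between the subjective measures of ETS and the objective measures (questionnaire versus biological analysis of nicotine in hair"). Phase 3 of the Statistical analysis section sets out how this will be done.

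- The questionnaire is reduced to "a summary evaluation of the questionnaire on a discrete, quantitative scale", which draws on "the number of smoking cohabitants, the number of cigarettes that they smoke and the exposure time outside of the home". No range, item weights, mean or SD are given.
- The other measure is hair nicotine, a concentration. The Sample size section reports that in the pilot "a mean of 6.83 ng/mg and a standard deviation of 8.88 ng/mg have been obtained".
- Three statistics are planned. The first is a correlation: "Pearson's (or Spearman's depending on the distribution) correlation coefficient will be calculated between the estimate and the result obtained in the nicotine hair analysis". The second is the statistic at issue: "The intraclass correlation coefficient will also be studied between both measures". For the third, both measures are dichotomised "into two categories (exposed/not exposed) and the Kappa coefficient between the two will be calculated".

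The two measures are put on a common scale only for the third statistic. For the second, the article names no form of the coefficient and no rescaling.

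**The concern.** An intraclass correlation treats its inputs as repeated measurements of one quantity in one unit. It counts differences in spread, and in the absolute-agreement form differences in mean, as disagreement. A score that combines people, cigarettes and time has no natural unit in common with ng/mg. Its mean and SD follow from the item weights that the investigators choose. Two teams could hold identical data, weight the score differently and report quite different coefficients.

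At stake is the reading of a secondary result. A low value could be taken as evidence against the questionnaire although the two measures track each other perfectly. A high value would partly reflect a lucky match of scales.

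**Working it through.** The article states no value for this coefficient, so there is no figure to reproduce. The check asks how far the coefficient moves when only the scale of the score changes.

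**Inputs.** Hair nicotine: mean m₁ = 6.83 and SD s₁ = 8.88 ng/mg (Sample size section, pilot of 46 babies). The score's mean m₂ and SD s₂, and the correlation r between the measures, are not in the document. They are assumptions, shown as ranges.

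**Formulas for two measures.**

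- Consistency: ICC = 2·r·s₁·s₂ / (s₁² + s₂²)
- Absolute agreement: ICC = 2·r·s₁·s₂ / (s₁² + s₂² + (m₁ − m₂)²)

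Because s₁² + s₂² ≥ 2·s₁·s₂, both forms are bounded by |r| and take its sign. Both depend on the ratio of the SDs, so choosing the other form does not remove the problem.

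**Case 1: perfect proportional relation** (r = 1, score = f × nicotine). Then s₂ = f·s₁ and m₂ = f·m₁, with s₁² = 78.85 and m₁² = 46.65.

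- f = 3, absolute: 6 × 78.85 / (10 × 78.85 + 4 × 46.65) = 473.1 / 975.1 = 0.485. Consistency: 6/10 = 0.60.
- f = 10, absolute: 20 × 78.85 / (101 × 78.85 + 81 × 46.65) = 1577.1 / 11742.9 = 0.134. Consistency: 20/101 = 0.20.

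| Scale factor f | Absolute | Consistency | Pearson, Spearman |
|---|---|---|---|
| 1 | 1.00 | 1.00 | 1 |
| 3 | 0.49 | 0.60 | 1 |
| 10 | 0.13 | 0.20 | 1 |

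**Case 2: strong but imperfect relation** (r = 0.8), nicotine in ng/mg, three assumed score scales.

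| Score mean/SD | Consistency | Absolute |
|---|---|---|
| 5 / 2.5 | 35.52 / 85.10 = 0.42 | 35.52 / 88.45 = 0.40 |
| 15 / 9 | 127.87 / 159.85 = 0.80 | 127.87 / 226.60 = 0.56 |
| 50 / 20 | 284.16 / 478.85 = 0.59 | 284.16 / 2342.50 = 0.12 |

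The correlation is the same in every row.

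**Case 3: simulation** (992 simulated babies, log-normal nicotine with the pilot mean and SD, discrete 0–10 score, assumed underlying correlation of 0.7). The ANOVA-based consistency/absolute values are 0.177/0.172. Multiplying the score by 10 changes them to 0.318/0.087. Pearson (0.422) and Spearman (0.674) do not change.

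**Does standardising help?** With both measures as z-scores, s₁ = s₂ = 1 and m₁ = m₂ = 0, so both forms reduce to r. In the simulation the standardised value is 0.422, equal to Pearson.

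**The case against.** The strongest defence is that the coefficient is an addition. The correlation comes first and kappa on a shared binary scale comes last, and neither depends on the units of the score. The objective can be answered without the intraclass correlation. This stands, and it limits the weight of the point.

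It can also be said that an analysis plan not shown here might specify standardisation. That is possible, but the result would only duplicate Pearson's correlation. The article as written commits to the coefficient between the two measures as they are.

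Three stronger readings are tempting, and the document does not support them.

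- *The coefficient will come out near zero.* In ng/mg, the unit that the article uses, the r = 0.8 illustrations run from 0.12 to 0.80. Values around 0.001 arise only if nicotine is re-expressed in pg/mg, which the article never does.
- *The coefficient says nothing but the choice of units.* It keeps the sign of r and cannot exceed |r|, so it carries some information about association. It cannot be read as a degree of agreement.
- *Kappa will be depressed because almost every baby is exposed.* The inclusion criterion ("Babies under 18 months of age whose parents answer affirmatively to the question" about smoking by themselves or a partner) requires a smoking parent, not an exposed baby. The Background cites at most 75% of smoking mothers exposing their newborns, and 47–60% of those babies with significant urinary cotinine. For a questionnaire with an assumed 90% sensitivity and specificity, kappa is 0.80 at 47%, 0.79 at 60% and 0.75 at 75% exposed. At 75%, for example, observed agreement is 0.90 and chance agreement is 0.75 × 0.70 + 0.25 × 0.30 = 0.60, so kappa = 0.30/0.40 = 0.75. A marked fall needs prevalences of 90–95%, which nothing in the document supports.

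**Conclusion.** The point holds in a limited form. As planned, the intraclass correlation compares quantities with no common unit. Between zero and |r|, its size is fixed by the undefined scale of the score. A perfect proportional relation can yield anything from 1.00 down to about 0.13 (absolute) or 0.20 (consistency) over a tenfold range of scale. Those figures rest on the pilot mean and SD and on assumed score scales; they illustrate the dependence and do not predict the trial's result. The algebraic dependence needs no such assumption.

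The consequence is one uninterpretable supplementary statistic for a secondary objective. It would be wrong to infer that the concordance objective fails, because the planned correlation and kappa still serve it.

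**What to change.** Delete the sentence on the intraclass correlation from phase 3, and base the concordance objective on the Pearson or Spearman correlation and the kappa already planned.

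If the investigators want to keep it, they should first define how the score is converted to ng/mg, and compute the coefficient on the calibrated values. The conversion should not be a linear regression fitted in the same babies. The fitted values would then have the same mean as nicotine and SD |r|·s₁, and both forms would reduce to 2r²/(1 + r²), again a restatement of r.

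A ROC curve of the score against a nicotine cut-off, or positive and negative percent agreement beside kappa, would be optional extras and are not needed to repair this point.

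The cost is a change of wording. No data collection, sample size or primary analysis is affected.
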